## Abstract

**Background:**

Aneurysmal subarachnoid hemorrhage (SAH) may be complicated by delayed cerebral ischemia, which is a major cause of unfavorable clinical outcome and death in SAH-patients. Delayed cerebral ischemia is presumably related to the development of vasospasm triggered by the presence of blood in the basal cisterns. To date, oral application of the calcium antagonist nimodipine is the only prophylactic treatment for vasospasm recognized under international guidelines.

In retrospective trials lumbar drainage of cerebrospinal fluid has been shown to be a safe and feasible measure to remove the blood from the basal cisterns and decrease the incidence of delayed cerebral ischemia and vasospasm in the respective study populations. However, the efficacy of lumbar drainage has not been evaluated prospectively in a randomized controlled trial yet.

**Methods/Design:**

This is a protocol for a 2-arm randomized controlled trial to compare an intervention group receiving early continuous lumbar CSF-drainage and standard neurointensive care to a control group receiving standard neurointensive care only. Adults suffering from a first aneurysmal subarachnoid hemorrhage whose aneurysm has been secured by means of coiling or clipping are eligible for trial participation. The effect of early CSF drainage (starting < 72 h after securing the aneurysm) will be measured in the following ways: the primary endpoint will be disability after 6 months, assessed by a blinded investigator during a personal visit or standardized telephone interview using the modified Rankin Scale. Secondary endpoints include mortality after 6 months, angiographic vasospasm, transcranial Doppler sonography (TCD) mean flow velocity in both middle cerebral arteries and rate of shunt insertion at 6 months after hospital discharge.

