### Subject Inclusion criteria

• Age: 18 years or older

• First aneurysmal SAH

• Pre-morbid modified Rankin Scale score 0 ("no symptoms at all") or 1 ("no significant disability despite symptoms")

• Aneurysm treatment performed during the first 48 hours after the initial hemorrhage.

• Informed consent by the patient or his/her legal representative. In case neither the patient is capable of giving informed consent nor a legal representative is available, informed consent can be given by an independent physician neither involved in the patient's treatment nor in conducting the trial.

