### Interventions

In order not to provoke premature rupture of the aneurysm due to accidental drainage, randomization to the study and eventual placement of a lumbar drain takes place after securing the aneurysm by the preferred method of choice (Figure 1). Every patient in the lumbar drainage group (LD-group) receives a lumbar drain during anesthesia required for the aneurysm treatment. Insertion of a lumbar drain into the subarachnoid space is conducted in standard fully sterile technique. This is to be performed before anticoagulation or anti-platelet therapy is initiated, which sometimes is warranted after endovascular coiling. A post-procedural CCT scan of the brain is performed within 24 hours after aneurysm treatment. In case of neurological worsening after the procedure it is strongly recommended to perform the follow-up CCT-scan as soon as possible.

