If the post-procedural CCT or any other follow-up CCT scan shows compressed basal cisterns or any signs of threatening herniation, lumbar CSF diversion in the LD-group must not be performed. It may still be feasible to carefully drain CSF via the lumbar route [14], but this is at the discretion of the local investigator and not recommended. In patients requiring sedation and mechanical ventilation, either due to neurological impairment or for other medical reasons, intracranial pressure monitoring is mandatory. This may be performed according to local policy either with parenchymal or ventricular devices. If the intracranial pressure exceeds 20 mmHg, further CSF drainage via lumbar route shall be interrupted until the ICP is below 20 mmHg again. Careful CSF-drainage via the lumbar route may still be feasible in case of high intracranial pressure [14], but again this is at the discretion of the local investigator. A method of detecting the safety of lumbar CSF diversion may be determining the gradient of lumbar versus intracranial CSF pressure [15]. Albeit promising, the Earlydrain investigators explicitly rate this approach preliminary and experimental. In case of doubt, lumbar CSF diversion must not be performed.

Further neuromonitoring with transcranial duplex sonography (TCD), electroencephalography (EEG), brain tissue oxygenation recordings, jugular bulb oxymetry, regional cerebral blood flow measurement, microdialysis or other methods is at the discretion of the center and according to its local guidelines. As far as possible, this data should be saved electronically for post-hoc analysis.

A CCT scan as well as conventional digital subtraction angiography (DSA), CT angiography or MR angiography for assessment of vasospasm in the larger vessels is routinely performed on day 7 to 10 after the initial hemorrhage, according to local guidelines. In case of the occurrence of a DND when vasospasm is assumed to be the cause, angiography may be performed at any time. If it is performed earlier than day 7 to 10 and the patient shows no clinical deterioration thereafter, the angiography on day 7 to 10 is omitted. Treatment of radiographically confirmed vasospasm is according to local guidelines and not specified in the Earlydrain study protocol. It may include augmentation of cerebral blood flow via hypertensive hypervolemia as well as endovascular balloon dilation or intraarterial infusion of vasodilators.

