After cerebrovascular imaging on day 7 to 10 the lumbar drainage of CSF is stopped in the LD-group. If cerebrovascular imaging is carried out before day 7, lumbar drainage is stopped on day 8. It may be pursued on a clinical base, as required.

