### Amount and duration of CSF drainage

Patients randomized to the lumbar drainage group shall receive a daily drainage of 120 ml CSF, or 5 ml per hour for seven days. If higher amounts of CSF need to be drained on clinical grounds as in patients with hydrocephalus, this is preferably performed via an external ventricular drain.

The drain is planned to remain in place until the control angiography on day 7 to 10 after the initial hemorrhage. The local investigator may decide to remove the drain earlier in patients fully mobilized without clinical necessity of CSF drainage. However, consecutive drainage should not be less than four days to achieve a valid study result. Lumbar CSF drainage may be prolonged beyond the control angiography on clinical requirement. The amount of CSF drainage may then be adjusted to clinical requirements and bears no further restriction.

Patients randomized to the control group should not receive a lumbar drain before the planned control angiography to be performed on day 7 to 10 after SAH. If the patient develops hydrocephalus, and no EVD was placed initially for CSF drainage, a lumbar drain may be installed at the discretion of the local investigator. These patients are analyzed in the intention-to-treat analysis, but are not suitable for the per-protocol analysis.

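### The Interventions section forbids lumbar drainage under threatening CT findings and in the next sentence leaves it to local discretion; secondarily, the seven-day duration does not match the stop rule counted from hemorrhage

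*Protocol article*

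**What the plan says.** **Safety limit.** In the Interventions section (text after the Figure 1 legend), if the post-procedural or any later CT scan shows compressed basal cisterns or signs of threatening herniation, "lumbar CSF diversion in the LD-group must not be performed". The next sentence allows that careful lumbar drainage may still be feasible and adds that "this is at the discretion of the local investigator and not recommended". For intracranial pressure above 20 mmHg, lumbar drainage is to be interrupted until the pressure is below 20 mmHg; a following sentence again leaves careful drainage at high pressure to the local investigator. The same paragraph ends by ruling out lumbar diversion where there is doubt. The section on safety of lumbar drains calls drainage a possible treatment even with compressed cisterns, then calls the risk unclear and tells investigators not to insert a drain in unclear cases.

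**Duration and stop.** The section on amount and duration specifies "5 ml per hour for seven days". The Interventions section stops drainage after vascular imaging on day 7 to 10, and adds: "If cerebrovascular imaging is carried out before day 7, lumbar drainage is stopped on day 8". The duration section counts the day 7 to 10 angiography from the hemorrhage. After allowing earlier removal in fully mobilized patients, it says "consecutive drainage should not be less than four days to achieve a valid study result".

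**Start.** The abstract refers to "early CSF drainage (starting < 72 h after securing the aneurysm". In the Interventions section every patient in the drainage arm "receives a lumbar drain during anesthesia required for the aneurysm treatment", a CT scan follows within 24 hours, and drainage begins after that scan. The inclusion criteria require "Aneurysm treatment performed during the first 48 hours after the initial hemorrhage".

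**The concern.** The safety wording matters most. A prohibition and a discretionary permission for the same finding lead to different conduct at different centres, and each centre can cite the protocol. A monitor verifying source data could not say whether lumbar drainage in a patient with compressed cisterns is a deviation. There is also an effect on the analysis. Read literally, the per-protocol rule in the Statistical Analysis section excludes patients whose lumbar drainage departs from 5 ml/h. A patient whose drain was withheld under the first sentence would be excluded, while a similar patient drained under the second sentence could stay in. These are among the sickest patients in the trial.

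On timing, the duration runs from the start of drainage and the stop runs from the hemorrhage. Two clocks agree only for certain combinations of start day and imaging day, so a centre can follow the stop rule and still deliver less than the stated course.

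**Working it through.** **1. Safety wording, set side by side.** No arithmetic applies.

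- CT finding (compressed cisterns or threatening herniation): first sentence, absolute prohibition; second sentence, local discretion with advice against.
- Intracranial pressure above 20 mmHg: first sentence, mandatory interruption; later sentence, local discretion, this time without the advice against.
- Tie-breakers: no drainage in case of doubt (Interventions); no insertion in unclear cases (safety section).

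The tie-breakers bind an investigator who is in doubt. One who is confident that careful drainage is feasible meets neither, and still has a sentence that forbids and a sentence that permits.

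**2. The plan's own exposure figure.** 5 ml/h × 24 h = 120 ml per day, as stated. Over seven days this is 7 × 120 = 840 ml.

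**3. Latest start.** The inputs are the treatment limit of 48 h after hemorrhage (inclusion criteria), a CT scan within 24 h of treatment with drainage started after it (Interventions), and the abstract's limit of 72 h after securing.

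- Body text: 48 h + 24 h = 72 h, about day 3.
- Abstract limit: 48 h + 72 h = 120 h, about day 5.

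The body figure takes drainage to start as soon as the scan is done.

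**4. Days of drainage = stop day − start day** (elapsed days, hemorrhage = day 0).

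| Start | Stop day 7 | Stop day 8 | Stop day 10 |
|---|---|---|---|
| Day 1 | 6 | 7 | 9 |
| Day 2 | 5 | 6 | 8 |
| Day 3 (latest, body text) | 4 | 5 | 7 |
| Day 5 (abstract limit) | 2 | 3 | 5 |

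A day-8 stop gives seven days only if drainage began within 24 h of the hemorrhage. A day-7 stop cannot give seven days, because drainage comes after both treatment and the scan. At the planned rate, the latest body start with a day-7 stop gives 4 × 120 = 480 ml, which is 480/840 = 57% of the seven-day volume; with a day-8 stop it gives 5 × 120 = 600 ml, or 71%.

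**5. Against the four-day minimum.** Every start within the body text reaches at least four days. At the abstract limit, day-7 and day-8 stops give 2 and 3 days and fall short; a stop on day 9 gives 9 − 5 = 4 days and meets it.

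**6. Day-count convention.** If the hemorrhage is counted as day 1, every entry falls by one day. The latest body start then gives 3, 4 and 6 days, and the abstract limit gives 1, 2 and 4.

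**The case against.** A reader might infer that the start, duration and stop rules cannot all hold. The documents do not support that. Seven days from a start on day 0, 1, 2 or 3 ends on day 7, 8, 9 or 10, which is the imaging window itself. If imaging is timed to the start, seven days and the stop rule are compatible for every start allowed by the body text. The mismatch that remains is that nothing links the imaging day to the start day, and the day-8 fallback is fixed.

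A reader might also infer that the plan generally lets exposure drop below its own four-day minimum. That too goes beyond the text. On elapsed days the shortfall needs the abstract's 72 h limit, whereas the body text places every drain during the treatment anesthesia. Insertion then, with drainage after a scan within 24 h, lies well inside 72 h, so a centre that follows the body also satisfies the abstract. The abstract is loose rather than contradictory. The four-day sentence is worded as a recommendation, follows the permission for early removal, and sits beside permission to prolong drainage on clinical grounds. Even so, no sentence says that the stop day gives way to the minimum.

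On safety, the cautions about doubtful and unclear cases do make the default restrictive. That narrows the practical ambiguity but does not remove the contradiction. A per-protocol criterion on duration may stand in an analysis plan that is not shown, so its absence from the article is not held against the plan.

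**Conclusion.** The main point stands on the text alone: two clinical triggers, compressed cisterns or threatening herniation on CT and intracranial pressure above 20 mmHg, each carry both a mandatory rule and local discretion, and the cautions elsewhere do not resolve it.

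The secondary point stands with limited size. At the latest body start, stops on day 7, 8 or 10 give 4, 5 or 7 days against the stated seven. The four-day minimum holds on elapsed days; it would fail by one day, for a day-7 stop at the latest start, only if the hemorrhage is counted as day 1. The documents give no distribution of start or imaging days, so the share of patients who would miss seven days cannot be estimated.

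The abstract's start window is a minor inconsistency. Its 72 h equals the body's outer limit counted from hemorrhage (48 h + 24 h), so a slip in the time anchor is possible, but that is an inference.

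None of this invalidates the intention-to-treat comparison, and the sample size does not depend on it. The point should be corrected because it concerns patient safety and uniform delivery of the intervention, and because the correction is cheap.

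**What to change.** 1. In the Interventions section, reconcile the prohibition and the discretion sentence for CT findings into one rule, and do the same for the intracranial pressure rule. Bring the section on safety of lumbar drains into line with the result.
2. Reconcile the seven-day duration with the stop rule: name one time anchor, state how days are counted, and say which statement governs when they differ, including how the stop day relates to the four-day minimum.
3. Align the abstract's start window with the start described in the Interventions section.

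Which clinical rule applies in each case is for the clinical investigators to decide; this review proposes none. The cost is a short protocol clarification and a memo to sites. The sample size and the primary analysis do not change.

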**Discussion:**

Here, we present the study design of a multicenter prospective randomized controlled trial to investigate whether early application of a lumbar drainage improves clinical outcome after aneurysmal subarachnoid hemorrhage.

**Trial registration:**

www.clinicaltrials.gov Identifier: NCT01258257

## Background

Non-traumatic subarachnoid hemorrhage (SAH) is a major cause of stroke accounting for approximately 1-7% of cases. In 80% of SAH-cases the source of bleeding is a ruptured cerebral aneurysm [1,2]. Important for a patient's prognosis is the severity of the initial bleeding and complications associated with the presence of blood in the subarachnoid space. Once the aneurysmal SAH has occurred patients are predominantly threatened by two distinct problems in the acute phase. First, they may experience a further, often more severe, hemorrhage, and second, they may suffer delayed neurologic deterioration (DND) caused by delayed cerebral ischemia (DCI). The consequences of DCI may either be transient or may result in cerebral infarction with persistent neurologic disability or death.

The first problem, aneurysmal re-bleeding, is solved through rapid cerebrovascular imaging and subsequent treatment of the ruptured aneurysm, thus preventing recurrent hemorrhage. Aneurysm treatment may be performed either via craniotomy and surgical clipping of the aneurysm or using endovascular techniques by occluding the aneurysm with small platinum coils.

The second problem, DCI, is more difficult to recognize and to handle. Patients after aneurysmal SAH experience DND with an incidence of 30 to 60% [3]. It may be caused by hydrocephalus, cerebral edema, fevers, seizures, electrolyte abnormalities, and DCI. Strongly associated with DCI/cerebral infarction is a constringency reaction of the vessels supplying the brain with blood, called vasospasm [4]. The pathomechanism leading to vasospastic vessel constriction is not completely understood [5] and the quantitative relevance of vasospasm for the development of DCI is less clear than previously assumed [6].

Clinical signs of DND accompanying radiographic vasospasm are variable, depending on the affected blood vessels including alteration of mental status, aphasia, hemiparesis, or any other focal neurologic deficit. Often the consequences of this condition may include permanent neurologic deficits and death due to infarction and subsequent herniation of the brain. DCI, DND and vasospasm may be causatively interlinked, but also be independently present from each other. Vasospasm may be asymptomatic without clinically apparent deterioration of the patient's condition or external circumstances, such as deep sedation, may prevent clinical detection of a deterioration caused by vasospasm.

As DND is unspecific concerning its etiology, clinical judgment, therefore, is unreliable for the prediction and recognition of vasospasm. Thus digital subtraction angiography is the procedure of choice for the detection of vasospasm. Vasospasm may be present in the proximal vessels, the distal branches of the vasculature, or both.

Currently the only measure recognized for the prevention of DCI is the prophylactic application of the calcium channel blocker nimodipine [7]. Newer approaches, to date not included in official guidelines but pursued in several centers, include medication with statins and magnesium [8].

One hypothesis claims that the likelihood of angiographic vasospasm to occur is related to the amount of blood in the basal cisterns. According to this consideration, one prophylactic strategy is to remove as much of this blood as early as possible. If clipping of the aneurysm is performed this can be achieved intraoperatively by opening the terminal lamina and irrigating the blood from the basal cisterns. Albeit promising, studies addressing the efficacy of this measure show inconclusive results [9]. This approach is not feasible if the aneurysm is secured using an endovascular approach.

Excess removal of cerebral spinal fluid (CSF) via an external ventricular drain fails to prevent vasospasm and may lead to a higher incidence of posthemorrhagic shunt dependency [10,11]. Supposedly this is because after aneurysmal SAH, the blood settles and clots in the basal cisterns and therefore only CSF, being more lightweight, is removed via the ventricular drain.

Application of a lumbar drain has been proposed as an alternative approach to address clotting of the blood in the basal cisterns. In two retrospective studies in patients after aneurysmal SAH, the safety of this approach was shown [12,13]. One of these studies addressed the radiologic and clinical outcome after surgical clipping [12], while the other addressed the outcome after endovascular coiling [13]. Both studies led to a markedly diminished incidence of angiographic vasospasm and improvement in clinical outcome measured by the Glasgow Outcome Scale (GOS). Therefore a prospective study addressing the efficacy of this novel approach is warranted and currently being conducted (EARLYDRAIN).

The aim of the EARLYDRAIN study is to examine the efficacy of application of lumbar drainage in patients with acute subarachnoid hemorrhage from a ruptured cerebral aneurysm. The hypothesis is that early application of a lumbar drain after aneurysmal SAH leads to an improved outcome at six months after the hemorrhage, measured by the modified Rankin score. Furthermore, it is hypothesized that this postulated clinical effect will be due to a diminished incidence of cerebral vasospasm and delayed cerebral ischemia. Therefore the incidence of angiographic vasospasm and the development of new infarctions shown on CCT at discharge of the patient will be among the secondary endpoints of the present study.

## Methods

### Study design

The present study is in compliance with the Helsinki Declaration. Ethical approval was obtained by the ethical committee of the medical faculty of the Friedrich-Alexander-University Erlangen-Nürnberg (reference number: 4171).

The EARLYDRAIN study is a 2-arm randomized controlled trial to compare an intervention group receiving early continuous lumbar CSF-drainage and standard neurointensive care to a control group receiving standard neurointensive care only. It is conducted by a German national study group consisting of neurosurgical centers treating at least 30 patients with aneurysmal subarachnoid hemorrhage per year. Data management and monitoring will be performed by the Center for Stroke Research Berlin (CSB) at Charité University Medicine, Berlin, Germany.

Patients suffering from an aneurysmal SAH and completed elimination of the causative aneurysm are being recruited for this study. The choice of the method of aneurysm treatment is at the discretion of the neurovascular team taking care of a patient and not specified by the study protocol. All medical treatment is performed according to local guidelines and standard operating procedures.

### Subject Inclusion criteria

• Age: 18 years or older

• First aneurysmal SAH

• Pre-morbid modified Rankin Scale score 0 ("no symptoms at all") or 1 ("no significant disability despite symptoms")

• Aneurysm treatment performed during the first 48 hours after the initial hemorrhage.

• Informed consent by the patient or his/her legal representative. In case neither the patient is capable of giving informed consent nor a legal representative is available, informed consent can be given by an independent physician neither involved in the patient's treatment nor in conducting the trial.

